## Abstract

**Background:**

Intensive interventions on smoking cessation increase abstinence rates. However, few electronic mail (E-mail) based intensive interventions have been tested in smokers and none in primary care (PC) setting. The aim of the present study is to evaluate the effectiveness of an intensive E-mail based intervention in smokers attending PC services.

**Methods/design:**

Randomized Controlled Multicentric Trial. *Study population*: 1060 smokers aged between 18–70 years from Catalonia, Salamanca and Aragón (Spain) who have and check regularly an E-mail account. Patients will be randomly assigned to control or intervention group. *Intervention*: Six phase intensive intervention with two face to face interviews and four automatically created and personal E-mail patients tracking, if needed other E-mail contacts will be made. Control group will receive a brief advice on smoking cessation. *Outcome measures*: Will be measured at 6 and 12 months after intervention: self reported continuous abstinence (confirmed by cooximetry), point prevalence abstinence, tobacco consumption, evolution of stage according to Prochaska and DiClemente's Stages of Change Model, length of visit, costs for the patient to access Primary Care Center. *Statistical analysis*: Descriptive and logistic and Poisson regression analysis under the intention to treat basis using SPSS v.17.

**Discussion:**

The proposed intervention is an E-mail based intensive intervention in smokers attending primary care. Positive results could be useful to demonstrate a higher percentage of short and long-term abstinence among smokers attended in PC in Spain who regularly use E-mail. Furthermore, this intervention could be helpful in all health services to help smokers to quit.

**Trial Registration:**

Clinical Trials.gov Identifier: NCT01494246.

## Background

Health effects among smokers and non-smokers of tobacco consumption are well-established including principally respiratory and cardiovascular diseases and cancer [1]; in fact is one of the leading preventable causes of death worldwide and mainly in occidental societies [2]. In Spain, for instance, smoking is the health problem that causes more mortality and morbidity [3], and therefore originates one of the higher health costs. According to the last national survey conducted in Spain in 2006 the percentage of daily smokers aged 16 or older was 26.44% [4]. The vast majority of smokers declare a willingness to quit smoking and approximately 60% have tried it [3], although only 3 to 5% of them per year accomplished smoking cessation [3,5,6].

Several cost-effectiveness studies worldwide have shown that both low and high impact care interventions to reduce tobacco consumption are cost-effective measured in cost per year of life gained and quality of life [3,7]. Moreover, under a public health view probably these interventions represent the most cost-effective method to improve population’s health. Minimum advice on quitting smoking among the general population achieves an average of 5% cessation per year [8,9]. In contrast, more intense interventions, can reach more than 20% of abstinence [10,11]; in general, it is well established that the more intensive the intervention, the best rates of smoking cessation are obtained [10]. The inclusion of those treatments that have demonstrated its efficacy in systematic reviews and metanalysis, has been confirmed to be useful [7].

Therapeutic intensive interventions for smoking cessation have been used in primary care, such as the one of the ISTAPS study [12], but none have been based in Information and Communication Technologies (ICTs). These interventions are based on the hypothesis that smokers that do not quit smoking but are aware of its harmful effects underestimate the health risk to due to its consumption [13]. So, these interventions could provide motivational feedback to promote risk awareness and accelerate changes on smoking behavior [14]. Some smokers who quit smoking have been identified as susceptible to damaging adverse effects of tobacco consumption or seen seriously threaten his or her health [15,16].

The vast majority of non-pharmacological use the Prochaska and DiClemente’s Transtheoretical Model of Change [17] that describes a succession of stages (precontemplation, contemplation, preparation, action and maintenance) each one indicating a different type of intervention. Other studies in our country have used this model among diabetic smokers patients attended in primary care and to confirm smoking abstinence using cooximetry [18] and another where information gathered by cooximetry is the main element to motivate smokers to quit [19].

The use of electronic mail and internet is increasing worldwide. In Spain, according to the National Statistics Institute, in 2010, 57% of households had Internet access; moreover there are 20 million estimated regular users and those who log at least once a week represent 58.4% of the population (7.1% increase over the previous year). Seventy-eight percent of the Spanish population between 16 and 74 uses the electronic mail, with an increase of those who access it via mobile devices [20].

Internet and E-mail use is also increasing in medicine and can be mostly useful in appointment citations and remainders, analytical results, computerized medical history, prescription refills, regular follow-up and access to health information. The advantages derived from professional-patient E-mail communication include: time and cost saving for hospitals, primary care centers, primary care professionals and patients (e.g. patients who frequently travel and sanitary professional of rural areas can easily contact with physicians and patients respectively) [21,22] and convenience since it does not have a simultaneous nature (the person can check the messages at his or her convenience) [21]. Several patients also refer that E-mail communication can facilitate the contact with the sanitary professional; in face to face interviews they could not feel enough comfortable to rise certain issues or may have forgotten to ask important questions. Some of them deem a useful and satisfactory use E-mail communication in a secure and private environment [21]. A revision undertaken on the impact of e-therapies, Hsiung concluded that E-mail tracking is useful if preceded by a personal and direct relationship with the patient [23]. Finally, in the global crisis context these types of interventions can diminish visits to the primary care center. Limitations comprise unwillingness to use the E-mail, perception of lack of time and experience to use the new technologies [21,24], an abuse by an overriding number of messages on non urgent matters, and the development of a private and secure website and a specific deontological code could increase the economic costs [25].

Internet use in quitting smoking is becoming more evident, since it is necessary to recruit more smokers to fight smoking regardless of race or culture [26]. Several studies have published about the virtual communities in this field [27] and internet as a support to phone lines (quitlines) [28]. It has been established that it is a way that enriches the sanitary professional-patient relationship and that the dissemination of patient’s successful experiences can improve their self-esteem and generate positive attitudes [25] although further research is needed [29].

The 2008 the Treating Tobacco Use and Dependence Guideline, pointed out that online tools to quit smoking are promising tools that have not achieved its own potential to undertake interventions; results have been shown to be only favorable if online interventions are developed in very complex programs or if were carried out when the help was more intensive among intervention groups than in controls. Nevertheless, it also encourages depending on those characteristics that needs to be improved [7]. In Spain, the National Committee to Prevent Smoking Cessation (CNPT in Spanish) also supports these types of interventions to help smokers to quit [3].

Characteristics of smokers who seek help on the Internet to quit smoking were female sex (59%) and younger individuals. Generally are subjects who are trying to quit smoking (53%) and search information on how or medication to quit, whilst those who have already quit search information on how to face abstinence [30].

Twenty studies have been found to be registered at Clinical Trial when using keywords: E-mail AND smoking, none undertaken in Primary Care environment with personalized follow-up (Clinical Trials, 2012). In 2010 the Cochrane library published a revision that included the most relevant articles on internet interventions for quitting smoking. Ten out of twenty compared an internet based intervention with others not based on this media. The revision concluded that personalized and interactive internet based interventions, especially if there is an individualized tracking, can be more effective than those standardized protocols on smoking cessation. However, long-term smoking cessation is less effective when using these interventions compared to other interventions [31].

Both, The *E*-*consulta* and the experience described by Wallwiener and collaborators in 2009 [22,40], allow to think that better service and satisfaction of primary care services will be achieved by reducing resources of primary care addressed to smoking cessation. If sanitary systems facilitated E-mail based interventions on smoking cessation, and other sanitary problems, costs could be reduced and medical care and patient and sanitary professional satisfaction could be improved.

## Methods/Design

### Study design

A randomized controlled multicentric trial to evaluate the effectiveness and the cost effectiveness of a clinical practice guide based intervention, based in six contacts (two face to face interviews and 4 E-mails), to obtain continued smoking abstinence at 6 and 12 months compared to brief advice in smokers attended in Primary Care.

### Study population

Inclusion criteria of participants will comprise: smokers (of at least one cigarette per day) aged between 18 and 70 years who have an electronic mail account and check it regularly (at least once a week) and can assure their participation in the study for a year.

Exclusion criteria will be based on certain medical conditions which could contraindicate the fulfillment of the intervention such as known terminal illnesses, severe mental diseases, addiction to other psychoactive substances, patients that have already started to quit smoking or those unwilling to participate in the study were excluded. Smokers who do not have an E-mail account or do no not check it regularly will also be excluded, as well as those smokers who do not wish to be followed via E-mail as prefer face to face contacts.

Written informed consent will be obtained from all subjects of both intervention (IG) and control group (CG) prior to its inclusion on the study.

### Recruiting process

#### Inclusion of sanitary professionals

Diffusion of the project will be made in all primary care centers of the study area through the Xarxa de Centres Sense Fum (network of smoke free centers) to obtain sanitary professionals (general practitioners and nurses) interested in recruiting patients for the study. Of those willing to participate we will select only those who are regular users of E-mail and will be asked to sign a participation commitment. Causes of refusal to participate will be recorded. Those professionals interested in participating will attend a two-hour formative activity where the aim, methods, intervention will be explained and will be trained in the management of project’s web page and cooximetry technique. Assistance to one of the ten formative activities scheduled at different times to facilitate professional attending will be mandatory to participate in the study.

#### Inclusion of participants and randomization

During the recruitment period (first semester of 2013), trained professionals of each primary health care centre (general practitioners or nurses) will invite to participate subjects who meet the inclusion criteria by random systematic procedures. Twice a week each professional will invite to participate the first two smokers aged 18 to 70 who consulted them for any reason. In order to follow the criteria specified in the CONSORT Guide, we will register for all the subjects invited to participate (included or not in the study) on the web page of the study: date of interview, professional who realizes the visit, age and sex of the participant, and consumption of tobacco. Causes of refusal to participate will be recorded. Written informed consent to participate in the present study will be asked to all the individuals who accept to participate. Afterwards, the system of randomization of patients in control and intervention group (1:1 ratio) will be centralized and computer generated. Figure 1 shows the flow chart of the study.

**Figure 1 F1:**
[figure not shown]
**Algorithm of the TABATIC study.** ** A confirmatory cooximetry in standard conditions will be done on those subjects that declare tobacco abstinence. * Those individuals who are not willing to fix the D-day (usually in contemplative and precontemplative stages) will be contacted only once via E-mail after a month of the first face to face interview to encourage them to quit smoking. The patient will be able to fix the D-day up to 15 days prior to the second face to face interview.

### Description of the intervention

#### Control group

Subjects assigned to the control group, once the motivating problem of the clinical visit had been solved, will receive a brief advice on quitting smoking. Three months after the intervention a second face to face interview will be done to this group to check tobacco abstinence.

#### Intervention group

The proposed intervention will consist in the application of the recommendations of Miltenberger [41] and an evidence-based practical clinical guideline of the Primary Care Division of the Catalan Institute of Health [42]. Both propose an intervention previous to the day the patient sets to stop smoking (D-day) to reinforce behavior, to follow the patient a week after the D-day since approximately 25% of smokers who attempt to quit relapse within the first week and an E-mail feedback to reinforce behavior, to praise positive achievements (such as cigarette consumption reduction) and provide simple corrective feedback when the patient does not perform the target behavior. The basic steps on the intervention are:

1. First face to face interview: In the first contact with the patient, sociodemographic and related to tobacco consumption variables will be collected using a structured face to face interview. E-mail tracking will be approximately set for those individuals in the preparation/action stage, according to the model defined by Prochaska and DiClemente.

2. First E-mail contact: Will be done the following day from the first face to face interview in order to establish the day the individual will stop smoking (D-day), the treatment (if needed), to assess and facilitate motivational support to achieve individual’s goal to quit smoking.

3. Second E-mail tracking: Will be done a week later of D-day to evaluate abstinence, tolerance and adverse effects of medication, difficulties in everyday life, and to control medication.

4. Third E-mail tracking: Will be done 10 to 15 days after D-day to evaluate abstinence, gained benefits, to prevent relapsed and to control medication.

5. Fourth E-mail tracking: Will be done a month after D-day to prevent relapsed and false securities, to evaluate obtained benefits and to control medication.

6. Second face to face interview: Will be done three months after D-day to finish the treatment, to emphasize the effort made and improvement in patient conditions and to stress and prevent possible relapses. On those who declare tobacco abstinence an analysis of exhaled carbon monoxide (CO) will be made by cooximetry in standard conditions to confirm it.

The six phases of the intervention will be made on those patients who fix the D-day by the same sanitary professional who made the first contact with the patient and usually is the one who gives him/her attention, independently if he or she is a general practitioner or a nurse. E-mail messages will be automatically created by an automatic system and will clearly specify the name of the patient, information on the visits, the D-day (if fixed) and the name of the sanitary professional. Besides, the above established E-mail tracking, other E-mail contacts will be made, if needed, in order to clarify subject’s possible doubts (such as medication queries). Nature of the E-mails of the intervention o the study is offered in Additional file 1.

Those individuals who are not willing to fix the D-day (usually in contemplative and precontemplative stages) will be contacted only once via E-mail after a month of the first face to face interview to encourage them to quit smoking. A specific E-mail message will be sent to those who refer a lapse. The patient will be able to fix the D-day up to 15 days prior to the second face to face interview.

The study web page will be developed and maintained by an external company that will also offer support during the intervention process. In order to ensure confidentiality, we will assign to each participant his/her user identification and password so he or she will be able to read the electronic messages and reply if necessary. Sanitary professionals will also have their own identification code and password and will have only access to their own patient’s information. Moreover the study web page will be accredited as secure web environment in accordance to the national current legislation.

Both groups, control and intervention, will be followed at six and twelve months after the intervention by phone. The calls will be made by trained monitors of an external company who will not know if the patient belongs to control or intervention group, and will include a brief structured questionnaire to know their tobacco consumption, their stage of change and tobacco abstinence. A confirmatory cooximetry in standard conditions will be done on those subjects that declare tobacco abstinence.

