### Outcome measures

#### Main outcome measure

Self reported ‘continuous abstinence’ defined by Hughes et al. 2003 [43] as *the abstinence between quit day and a follow*-*up time* (at six and twelve months) after intervention confirmed by a breath CO cooximetry concentration of 6 parts per million (ppm) or less in standard conditions.

*Other outcome measures*:

– Point prevalence abstinence according to Hughes et al. 2003 [43] defined as *prevalence of abstinence during a time window immediately preceeding follow*-*up* at three, six and twelve months after intervention confirmed by breath carbon monoxide cooximetry in standard conditions.

Self reported tobacco consumption at three, six and twelve months after intervention: daily consumption in cigarettes/day.

– Self-reported reduction of daily tobacco consumption in cigarettes/day when the subject does not stop smoking at three, six and twelve months after intervention.

– Change of stage in the Prochaska and DiClemente's Stages of Change Model at three, six and twelve months after intervention.

– Prescription of tranquilizers, antidepressants, NRT (nicotine replacement therapy), at the beginning and end of the intervention and six and twelve months post intervention.

– Registered use of sanitary services in primary and specialized care, both in public and private settings.

– Time used by professionals in the two face to face interviews (initial and three months visits).

– Time used by sanitary professionals in case they have to answer E-mail contacts.

– Time used by patients in case they have to ask questions during the E-mail intervention.

– Costs for the patients to access Primary Care service at three, six and twelve months after intervention.

*Independents*:

– Type of intervention: Intensive counseling by E-mail vs brief advice.

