At six and twelve months after intervention all participants will be asked by phone about some variables related to tobacco consumption and stage of change in the Prochaska and DiClemente's Stages of Change Model (described above) by trained monitors. Moreover, at twelve months after intervention, level of satisfaction, acceptance of intervention, number of E-mail messages written and number of replies and level of social support during the intervention measured by PIQ Test will be recorded.

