### Sample size

Accepting an alpha risk of 0.05 and a beta risk of 0.20 in a bilateral contrast, 1060 individuals are needed; 530 individuals in the IG and 530 in the CG in order to detect a difference of at least a 5% among both groups. A continued abstinence of 5% was assumed for the non intervention group and a dropout rate of 20% is estimated. The sample size calculations were performed with the Granmo program (version 7.1).

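### The protocol contradicts itself on whether intervention patients who never fix a D-day have the three-month assessment, so secondary three-month outcomes could be missing by readiness to quit in one arm only

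*Protocol article*

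**What the plan says.** **Intervention arm** (Description of the intervention, Intervention group). The last of six listed steps reads "Second face to face interview: Will be done three months after D-day to finish the treatment". The text after the list says "The six phases of the intervention will be made on those patients who fix the D-day". Patients unwilling to set a date, described as usually contemplative or precontemplative, get a single E-mail one month after the first interview. The same paragraph and the Figure 1 legend let a patient set the D-day as late as 15 days before the second interview.

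**Control arm** (Control group): "Three months after the intervention a second face to face interview will be done to this group to check tobacco abstinence". No readiness condition applies.

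**Three-month outcomes** (Outcome measures, all secondary). Point prevalence abstinence, cigarettes/day, reduction, stage of change and patient access costs are listed at three months without restriction, for example "Self reported tobacco consumption at three, six and twelve months after intervention: daily consumption in cigarettes/day". Data collection places the three-month smoking items at the second interview and limits that interview neither by arm nor by D-day.

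**Later follow-up** (Data collection): "At six and twelve months after intervention all participants will be asked by phone". The Intervention group section likewise says that both groups are telephoned at six and twelve months.

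**Analysis** (Statistical methods). All analyses are by intention to treat, with a repeated-measures ANCOVA among the methods.

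**The concern.** The second interview does two jobs: it closes treatment in the intervention arm, and it is the only stated source of three-month smoking data in both arms. Access to the treatment job appears to depend on setting a quit date. If access to measurement follows it, controls at every level of readiness are measured, but intervention patients only if they were ready to name a date.

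Readiness is a post-randomisation selection factor here and is plausibly tied to smoking behaviour, so such missingness would not be ignorable and would arise in one arm only. At stake are the secondary three-month outcomes and the three-month time point of any repeated-measures model that uses them.

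**Working it through.** **1. The passages side by side**

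| Source | Intervention patient without a D-day | Control |
|---|---|---|
| Intervention group, step 6 | Visit dated from a D-day that does not exist | – |
| Intervention group, text after the list | Full six phases for those with a D-day; one E-mail for the others | – |
| Same paragraph and Figure 1 legend | D-day deadline counted back from the second interview, so a visit is presupposed | – |
| Control group | – | Visit for the whole group |
| Outcome measures; Data collection | Three-month items, unrestricted | Same |

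The first two rows point to no visit; the third and fifth point to one. No passage says when the visit falls for an intervention patient who never sets a D-day. The deadline is also circular: it is counted back from a visit that is itself dated from D-day.

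**2. The plan's own figure.** Inputs from Sample size: two-sided alpha 0.05, power 80%, control rate 5%, a gain of 5 percentage points (so 5% against 10%) and 20% lost. The section states "Accepting an alpha risk of 0.05 and a beta risk of 0.20 in a bilateral contrast, 1060 individuals are needed". By the arcsine formula, n = 2(1.960 + 0.842)² / [2(arcsin√0.10 − arcsin√0.05)]² = 423.7, so 424 per arm. Then 423.7/0.80 = 529.7, so 530 per arm and 1060 in total. The sample size reproduces and is not at issue. The 424 is used below.

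**3. Illustration: abstinence, attenders only.** Assumptions that the protocol does not supply: no true effect; 5% abstinent at three months in each full arm (borrowed from the continued-abstinence assumption); 424 controls seen; 424f intervention patients seen, where f is the share fixing a D-day; abstinence q of 0 to 2% in the rest.

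Abstinence among those seen is p = [0.05 − (1 − f)q]/f, and the spurious difference is d = p − 0.05. The chance of rejection at two-sided 5% is Φ[(d − 1.96s₀)/s₁] + Φ[(−d − 1.96s₀)/s₁], where s₀ is the pooled and s₁ the unpooled standard error.

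Example, f = 0.5 and q = 0: p = 0.10, d = 0.05, pooled proportion 0.0667, s₀ = 0.0210, s₁ = 0.0232. The chance of rejection is 0.65.

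| f | Spurious difference (points) | False-positive rate | Intervention arm if unseen count as smokers |
|---|---|---|---|
| 0.9 | 0.3–0.6 | about 6% | 4.8–5.0% |
| 0.7 | 1.3–2.1 | 12–23% | 4.4–5.0% |
| 0.5 | 3.0–5.0 | 34–65% | 4.0–5.0% |
| 0.3 | 7.0–11.7 | 75–97% | 3.6–5.0% |

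The last column is f × p. With everyone kept and unseen patients counted as smokers, the upward bias disappears; the arm is at or slightly below its true 5%.

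**4. Illustration: cigarettes/day, unadjusted means.** Further assumptions: SD 9, and patients who fix a D-day smoke g fewer cigarettes/day than the others. The spurious difference is (1 − f)g, with standard error 9√(1/424 + 1/(424f)). For g = 2, f = 0.7 gives 0.6 with standard error 0.68 and 14% rejection; f = 0.3 gives 1.4 with standard error 0.91 and 34% rejection. For g = 4 the range is 42% to 87%. Counting unseen patients as smokers does not supply their consumption, reduction or stage.

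**The case against.** A reader might infer that the visit is definitely withheld from patients without a D-day, so that the three-month results necessarily compare all controls with the readier part of the intervention arm. The documents do not support that.

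- The quoted sentence goes on to say who delivers the package, and it cannot be applied step by step: the first interview and the first E-mail come before any D-day.
- The single-E-mail rule limits E-mail contact and does not expressly cancel a visit.
- The 15-day deadline and the unrestricted data collection text both suggest a visit for everyone. Figure 1, which is not shown, may settle the matter.
- Intention to treat is stated for all analyses, so an attenders-only abstinence comparison is not what the protocol plans.
- The error rates rest on assumed inputs. Those for cigarettes/day also use raw means, whereas baseline consumption and stage are collected and adjustment is planned, which would remove at least part of a pre-existing gap. For change of stage the direction is uncertain, since readier patients start further along.

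All of this stands and narrows the point. It does not remove the contradiction. Steps three to six are all dated from or after D-day, and the disputed visit is one of them, so a site working from the intervention steps has no instruction to book it for these patients. Intention to treat can protect abstinence, but it cannot recover consumption or stage that was never recorded.

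**Conclusion.** The contradiction is real and should be resolved; the stronger reading is only one way of taking the text. If sites follow the intervention steps literally, cigarettes/day, reduction and stage of change at three months would be missing from the less ready intervention patients and from no comparable controls. Abstinence would be biased upward only if unseen patients leave the denominator.

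The size cannot be fixed from the protocol, because the share setting a D-day is not given: the effect is negligible if nearly all do and large if few do. The tables show sensitivity and are not estimates of what will happen. Only secondary outcomes are touched. The main outcome at six and twelve months comes from telephone follow-up of both groups regardless of D-day. A reader might conclude that the three-month comparisons should be dropped; that is not needed, since a clarification preserves them.

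**What to change.** Reconcile the Control group, Intervention group (step six and the text after the list) and Data collection sections. State that the three-month outcome assessment, as distinct from treatment step six, is done for every randomised patient in both arms whether or not a D-day was fixed. Count it from a date that is defined for all of them, and keep all randomised patients in the denominator for three-month abstinence. This concerns outcome measurement only and leaves the content of treatment as it is.

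The cost is about one sentence of protocol text and a three-month contact for intervention patients without a D-day, which controls already have.
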